## 4.4 Screening assessment

Researchers will work with senior nursing staff of three CCU’s for a 3-week period prior to the intervention start date to identify those residents who might meet criteria for the study. After verbal consent is provided, an assessment of inclusion/exclusion criteria will commence. Participants who meet all inclusion criteria and none of the exclusion criteria will be invited to participate in the study and the formal consent process will commence. For those who consent to participate, they will be enrolled in the study and randomized.

Prior to randomisation, all participants recruited to the study will be assessed for baseline characteristics regarding: primary and secondary mental health diagnosis using DSM V by the Consultant psychiatrist on the research team, a range of sociodemographics (age, gender, employment, education, income, ethnicity), medication use – number and type of medications and chronic health conditions. Doses of antipsychotics will be converted to chlorpromazine equivalents using standardised measures (39).

# Participant Information and Informed Consent

Eligible participants (18-64 years) will be given a full explanation in lay terms, with a friend or family member present if desired, of the study aims, the discomfort, risks and benefits in taking part and a copy of the Participant Information Sheet Consent Form to review.

If the participant meets criteria to enter the study and has capacity, then informed written consent will be obtained. It will be explained to participants that they can withdraw from the study at any time without prejudice and will not affect their current care. The participant will have the opportunity to ask questions. A telephone number will be provided so that participant can call a research representative who will be able to respond to any questions they may have.

Each participant will acknowledge receipt of this information by giving written informed consent for participation in the study. A notation that written informed consent has been obtained will be made on the participant’s Case report Form (CRF). The original, completed consent forms will be retained by the Investigator and a copy will be provided by the research staff to the participants.

# Study Assessments and Procedures

Trained research assistants, who are blind to group membership, will conduct all assessments.

Measures conducted *at baseline only*, prior to randomisation:

Previous exercise experiences and history, exercise preferences, barriers and enablers to exercise will be assessed using Preferences, Barriers and Motivators questionnaire (40-42). Participants will be specifically asked the type of exercise they would prefer (RT or MIIT, or no preference) prior to randomisation. Self-report exercise will be obtained via the SIMPAQ, which is a researcher-administered self-report questionnaire assessing time (average minutes and hours) spent in bed, sitting or lying down, napping during the day, walking, structured exercise, and incidental activities completed in the previous week that has recently undergone an international validation study and correlated with objective physical activity that has undergone recent validation in people with severe mental illness (43).

Participants will be asked to wear to a GENEActiv wrist-worn accelerometer, (GENEActiv, Kimbolton, UK) for 5 days at baseline to measure habitual physical activity. Accelerometers have been shown to be acceptable for people with mental illness (44) and the most preferred way for measurement of physical activity by people with SMI (45). There is scant data regarding minimum wear time in people with SMI, however prior studies in the general population indicate 3.4 days is sufficient in the general population to assess habitual physical activity (46, 47). Habitual sedentary behaviour and walking activity will be measured each day the accelerometer is worn.

The accelerometer will record how many minutes per day each participant is sedentary and engages in light, moderate and vigorous physical activities. A recording is made of each 60-second period (defined as an ‘epoch’), and this is classified as being either sedentary, light, moderate or vigorous physical activity. Cut points have been defined according to metabolic equivalents (METs) of sedentary (<1.5 METs), light (1.5–3.99 METs), moderate (4.00–6.99 METs) and vigorous (>7+ METs), based on standardised algorithms with high sensitivity and specificity with oxygen consumption (48). Habitual physical activity will be measured as time spent in physical activity (minutes per day in light, moderate and vigorous activity) and total minutes of sedentary behaviour per day.

A battery of validated clinical and physical measures will be *conducted both at baseline and endpoint, week 8*. Baseline assessments will be conducted prior to randomisation:

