**Feasibility Criteria**

Recruitment – percentage of participants who consent to the study as a proportion of CCU residents who are referred from the three sites. Recruitment into exercise trials for people with SMI can be highly variable, however > 50% (majority) will be considered feasible.

Retention – the proportion of participants consenting to the trial who complete follow up assessments at 8 weeks as a proportion of the total number allocated in each condition. Feasibility will be defined as > 65% based on previous research (49).

Participation – the number of supervised exercise sessions attended by participants in each condition (RT and AIT group) as a proportion of total available sessions (3 sessions per week for 8 weeks - 24); feasibility will be defined by attendance at greater than 60% of sessions (15 sessions).

Participants will be evaluated at baseline and end point week 8. Total duration of the study will be 8 weeks. All outcome raters will be blind to outcome allocation, however blinding of participants to their exercise condition will not be possible.

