**7.1.3 Fidelity**

A one day training program for AEP’s at each CCU will be conducted in order to train them in the specific delivery of the intervention such that participant programs will be standardised for each condition and conducted in accordance with the protocol. Programs will be developed for individuals by each AEP at the CCU and reviewed by the AEP from the research team each week to ensure sessions from each condition are conducted within the scope of the intervention. This will include; terms of number of repetitions, progression, and any necessary adaptation for pre-existing musculoskeletal conditions if present.

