**7.1.5 Randomisation Procedure and blinding**

Participants will be randomised once written consent has been obtained and the baseline assessments have been completed.

Participants will be assigned a unique code that will be sent to an independent biostatistician for randomisation using a computer -generated sequence of numbers. Randomisation to either RT or MIIT condition, will occur in a 1:1 ratio, using block randomisation.

Once randomisation has occurred, participants will be notified of their group allocation by an independent staff member to ensure the research team remains blinded to allocation.

There will be no opportunity to change conditions once randomised, however if participants wish they may withdraw from the study and continue to exercise using the equipment and AEP at each CCU independently from the study. If withdrawal occurs, reasons for doing so will be recorded in the CRF. Following randomisation, participants will be asked whether they are happy with the condition they have been randomised to, and this will be recorded in the CRF.

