## Time Period, Frequency, and Method of Detecting AEs and SAEs

All adverse events will be recorded between the time of consent and the follow-up visits. Each Participant will be monitored regularly by the investigator and study personnel for adverse events occurring throughout the study. The research team will enquire about AEs by asking the following non-leading questions:

At the beginning and post intervention participants will be asked:

*“How are you feeling?” Does your current intervention cause you regular side effects? Do you have any general health conditions that cause you problems on a regular basis (e.g. that we might expect to occur over the duration of this study?"*

At subsequent scheduled visits, participants will be asked:

*“Since your last visit, have you had any health problems?”*

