# Data Management

A screening log will be utilized to track potential participants and also record the counts of individuals approached, consented, meeting inclusion/exclusion criteria, withdrawals, and completion (in keeping with standard CONSORT diagram requirements).

The Case Report Form (CRF) will comprise of the hard copy questionnaires, clinical assessments and measures. These de-identified data will be retained in a secure room, in a locked filing cabinet at Queensland Centre for Mental Health Research.

De-identified data from the CRFs will be entered into a spreadsheet that is stored on a password protected Queensland Health computer, which only members of the research team will have access to. Delegated research assistant will be trained in, and responsible for, entering data into the database. A copy of the PICF will be stored in a secure room in a locked filing cabinet separate from the CRFs at Queensland Centre for Mental Health Research.

All data will be exported into SPSS software to enable statistical analysis.

GENEActiv accelerometer data will be downloaded at completion of baseline and analysed in Matlab 2016a (The MathWorks, Inc., Natick, Massachusetts, United States) on a password protected Queensland Health computer.

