## Participant Reimbursement

Participants will be reimbursed for out of pocket expenses, inconvenience and time involved by the provision of either prepaid gift cards (e.g. Coles-Myer, K-Mart etc) or a Garmin Vivofit wearable device (value ~ $80) at the beginning of the intervention, the choice will be theirs. We will provide a $20 gift card to those who verbally assent to complete the SEES questionnaire before and after a single session of exercise in week 3 of the intervention. We will provide a $40 gift card on completion of the baseline assessment and at the end of study assessment (total reimbursement $100). If the study is terminated by the Investigator prior to completion, or a participant withdraws or is withdrawn from the study before completion, a pro-rata payment will be made at the discretion of the Investigator.

Participants will be given an opportunity to participate in a small group interview at the end of the intervention and will be reimbursed a $20 gift card for inconvenience and time involved.

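### The protocol contradicts itself on who is blind and leaves the rater blind unprotected for the interview-rated secondary outcomes at week 8

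*Protocol*

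**What the plan says.** **Who is blind.** The Protocol describes the trial as single blind and makes three statements about blinding, each of different scope.

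- Study Design, Feasibility Criteria: "All outcome raters will be blind to outcome allocation, however blinding of participants to their exercise condition will not be possible".
- Section 6, Study Assessments and Procedures: "Trained research assistants, who are blind to group membership, will conduct all assessments". No exception is named.
- Section 7.1.5: "participants will be notified of their group allocation by an independent staff member to ensure the research team remains blinded to allocation".

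**What the blind staff are asked to do.** SEES is item 10 in the section 6 list of measures, and Table 1 schedules it in weeks 3 and 8. Section 16.4 offers a gift card to those who agree to "complete the SEES questionnaire before and after a single session of exercise in week 3 of the intervention". Section 7.1 places the sessions on site in each unit's courtyard. Sections 7.1.1 and 7.1.2 give weights, bands and kettle bells to the resistance arm, and a bike, treadmill and boxing equipment to the aerobic arm.

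**What the research team does.** Under section 7.1.3, individual programmes are "reviewed by the AEP from the research team each week to ensure sessions from each condition are conducted within the scope of the intervention". Section 8.3 says: "The research team will enquire about AEs by asking the following non-leading questions", and one of those questions concerns side effects of the current intervention.

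**What goes into the case report form.** Section 12 says: "The Case Report Form (CRF) will comprise of the hard copy questionnaires, clinical assessments and measures". After randomisation, "participants will be asked whether they are happy with the condition they have been randomised to, and this will be recorded in the CRF" (section 7.1.5). Withdrawal reasons and adverse events attributed to the intervention are also recorded there. A research assistant enters the data.

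**The concern.** BPRS and SANS are scored from interviews, and WHODAS 2.0 is administered by an interviewer. Participants know their arm, so rater blinding is the only masking that supports the single-blind label. If a rater knows the arm, expectation can enter the scores. The week-8 comparison of resistance with aerobic training on symptoms and functioning would then be hard to interpret.

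The stated safeguard is that someone independent tells the participant the allocation. That protects the moment of notification only. The Protocol then assigns post-randomisation tasks to the same broadly described blind staff, and some of those tasks sit close to arm-revealing information. It also makes a team-wide claim of blindness that another section contradicts.

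**Working it through.** The Protocol gives no figure on this point, so the check sets its statements side by side.

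**1. Is the whole research team blind?** Section 7.1.5 says so. Section 7.1.3 has an exercise physiologist from the research team check each week that sessions in each condition stay within scope, which cannot be done without knowing the condition. The two statements cannot both be true. This step needs no inference.

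**2. Does the section 6 rule cover SEES?** SEES is listed among the measures in section 6 and appears in Table 1. The rule covers all assessments without exception, so by the text SEES falls to the blind research assistants.

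**3. Is SEES tied to a session?** For week 3, yes (section 16.4). For week 8, the secondary objectives and endpoints also speak of responses to a single session. The sessions are openly held and the equipment differs by arm. The blind staff are therefore given a task next to an activity that shows the arm. The gap to the final ratings is week 8 − week 3 = 5 weeks.

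**4. Is there a barrier between that task and the week-8 ratings?** None is described. The text does not separate SEES staff from raters, fix the order of SEES and the rated scales at week 8, or keep condition-related case report form pages from raters. It does not say that the data-entry assistant is a non-rater.

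**5. Adverse-event questions.** Section 8.3 gives these to the research team. Table 1 gives them to the exercise physiologist, and section 6.1.1 to the investigator or exercise physiologist. The documents disagree on who asks. Only the section 8.3 reading could bring a rater into the conversation.

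**6. Which outcomes are exposed?**

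| Outcome | Depends on a blind rater? |
| --- | --- |
| Recruitment, retention, attendance (primary) | No, these are counts |
| BPRS, SANS, WHODAS at week 8 (secondary) | Yes, by interview |
| Physical tests given in both arms (secondary) | Less so, but carried out by the same assessors |

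The 12-repetition-maximum strength test is given in the resistance arm only and is a further possible route. Steps 1 to 4 do not depend on it.

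**The case against.** The strongest reply is that a missing safeguard is not a broken blind. Most of it stands:

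- A reader might infer that the assistants do learn the arm at week 3. The Protocol does not say who hands out SEES or where, or that anyone watches the session. Its domains are wellbeing, distress and fatigue, not exercise type. Section 6 speaks of assistants in the plural, so one could give SEES and another rate at week 8.
- A reader might infer that all 50 participants are exposed. SEES at week 3 is limited to those who agree to it, so 50 is a ceiling and the actual number is not fixed.
- A reader might infer that the case report form reveals the arm. The satisfaction entry need not name it, and nothing says that raters see those pages.
- A reader might infer that the trial's hypothesis pushes raters towards resistance training. Section 11.1 hypothesises only that it is feasible and acceptable. The question of benefit is a secondary objective.
- Acceptability is described as assessed after completion of the trial, although Table 1 lists it in the week-8 column. The order left open is mainly that of SEES.
- Anchored BPRS scoring and the interview guides limit rater drift, whatever the rater knows.
- The Feasibility Criteria text already confines the blinding claim to outcome raters, and the reviewing exercise physiologist is never called a rater.

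The reply does not remove two things. Sections 7.1.5 and 7.1.3 contradict each other. Section 6, followed as written, puts blind assessors on a session-tied task with nothing to keep them apart from the later ratings.

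**Conclusion.** The point holds as a contradiction in the text and an unprotected blind. It does not establish that unblinding will occur. The statement that the research team remains blind is false as written. The rule on assessments literally assigns to blind staff a task beside arm-revealing sessions, five weeks before BPRS, SANS and WHODAS are rated.

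The size of any rating bias cannot be derived from the Protocol, and no planned data item would reveal a breach. Only secondary outcomes of an exploratory trial are affected. The conclusion rests on reading the section 6 rule as covering every listed measure, and on the absence of any stated separation of roles. If SEES staff and raters are separate in practice, the remedy is simply to say so.

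**What to change.** 1. In sections 6 and 7.1.5, limit the blinding claim to the staff who rate BPRS, SANS, WHODAS and the physical tests common to both arms. This agrees with the Feasibility Criteria text. Drop the claim that the research team as a whole is blind.
2. State that SEES is handed out and collected in weeks 3 and 8 by someone who does not rate week-8 outcomes. The exercise physiologist running the session could do this, with a sealed envelope.
3. At week 8, complete the rated and physical outcomes first. SEES, the acceptability questionnaire and adverse-event questions follow.
4. Keep adverse-event, withdrawal and allocation-satisfaction pages apart from the forms that raters hold.
5. Optional: have the rater record a guess of the arm after the week-8 ratings.

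The cost is Protocol wording, form layout and task assignment. No new staff are needed, because exercise physiologists who know the arm already supervise every session. One downside is that SEES answers collected by the trainer may be slightly more favourable; the sealed envelope limits this.

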**Measures include:**

1. WHODAS 2.0 –a reliable and valid assessment instrument for health and disability in all adult populations across different cultures, which covers six domains of functioning including cognition, mobility, self -care, getting along, life activities and participation. It is a 36 item questionnaire and will be interviewer administered.
2. Psychiatric symptoms will be measured using the Brief Psychiatric Rating Scale (BPRS) through the use of a semi-structured interview guide and an anchored scoring version of the BPRS-A. The BPRS was developed for efficient and comprehensive assessment of change across a broad range of psychiatric symptoms, is brief, reliable and sensitive and has been used extensively across a variety of settings and patients (1, 2).
3. Negative symptoms will be measured by the Scale Assessment of Negative Symptoms (SANS), a reliable and valid scale, using the Interview guide for Assessment of Negative symptoms (IG-SANS) (53-55).
4. Motivation to exercise; The Behavioural Regulation in Exercise Questionnaire (BREQ3) is a 24-item questionnaire used to assess amotivation, and external, introjected, identified, integrated and intrinsic behavioural regulations for exercise (four questionnaire items for each behavioural regulation subscale). Scoring is on a 5-point Likert scale ranging from 0 ('Not true for me') to 4 ('Very true to me'). BREQ-3 has high test-retest reliability (ρ>0.7) and has been shown to be moderately predictive of exercise participation (56).
5. Physical capacitywill be measured using three tests; the six-minute walk test (6MWT), which is a submaximal test to assess functional capacity that is commonly used for adults with mental illness (3). The 6MWT involves the participant walking as far as possible back and forth along a flat 20 m surface in six minutes; the tester provided standardised encouragement every minute consistent with guidelines (4).
6. The 30-second sit-to-stand-to-sit test will be used to assess lower body strength, for which participants were asked to stand up from a seated position and sit back down as many times as possible without using their arms in 30 seconds. The 30 second test has no ceiling and hence can be used in participants with a wide variety of ability levels. This test has been shown to correlate well with a 1-RM (one repetition maximum) leg-press test in community dwelling older adults (r>0.7), and hence suitable for our untrained participants, and has good test-retest reliability (59).
7. Grip Strength will be measured using a dynamometer. Maximal isometric handgrip is considered suitable for a variety of clinical settings and provides a simple and valid proxy of upper body muscular strength (19, 60).
8. Strength will be measured using the 1 minute AMRAP push up test – in which participants are asked to perform as many push ups as they can in one minute. At baseline, participants may choose to perform push ups from the knees, as a full body push up, or against a wall incline, depending on baseline conditioning. The push up test will be repeated in week 8 as the same format as was selected at baseline, ie if they select full body push ups at baseline, this will be repeated at week 8 (5).
9. Physical health measures will include; blood pressure will be taken manually with a sphygmomanometer in a seated position after 5 min of rest. An appropriate cuff size will be selected for each participant based on arm circumference. Height will be measured to the nearest 0.1 cm using a stadiometer, and weight will be measured to the nearest 0.01 kg using electronic scales (Charder MS 6111). Waist circumference will be measured at the mid-point between the iliac crest and lower ribs to the nearest 0.1 cm using a tape measure that provides 100g of tension. Body Mass Index (BMI) will be calculated (weight/health2).
10. Subjective Experience of Exercise Scale (SEES) (61) in week 3 (once competence has developed) and week 8 (at the end of the intervention). The SEES consists of 12 items that measure global psychological responses to the stimulus properties of exercise with items being determined to sit on three domains – psychological wellbeing, psychological distress and fatigue. The three subscales have been determined to have good internal consistency (62).
11. Strength – the 12RM will be measured pre and post the intervention in large muscle groups – squat and chest press, in the RT group only (due to the complexity of the testing).

Following *completion of the trial, acceptability* will be assessed:

Participants will be asked to complete a short self-report questionnaire regarding their exercise experiences at the end of the 8-week intervention. Responses will be reported on a 5 point Likert scale, with answers from Strongly disagree, disagree, neutral, agree and strongly agree.

For those willing to participate, acceptability will also be assessed via qualitative interviews. Participants from the intervention condition (Resistance Training, RT) will be invited to engage in an individual 20-minute semi-structured interview with a researcher not involved in the delivery of the intervention. The interview will cover topics including likes, dislikes, effectiveness and recommendations for future iterations. For those participants who consent Interviews will be audio-recorded on a dictaphone and uploaded to a password protected Queensland health computer. They will be de-identified and sent to a professional transcription company to be transcribed into written content, coded as interviewer and interviewee. Data will be analysed using thematic analysis to determine key themes identified by participants (6).

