**Table 1:**

**Schedule of Visits and Assessments**

| **Visit** | 0  Screening  Phase | 1  Baseline | 2 | 3 | 4 | 5 | 6 | 7 | 8 | 9 |
| --- | --- | --- | --- | --- | --- | --- | --- | --- | --- | --- |
| **WEEK** |  | 0 | 1 | 2 | 3 | 4 | 5 | 6 | 7 | 8 |
| **SCREENING AND CONSENT** |  |  |  |  |  |  |  |  |  |  |
| Informed consent | x |  |  |  |  |  |  |  |  |  |
| Ongoing capacity | x |  |  |  |  |  |  |  |  |  |
| Inclusion / exclusion criteria | x |  |  |  |  |  |  |  |  |  |
| Baseline demographics | x |  |  |  |  |  |  |  |  |  |
| **SAFETY** |  |  |  |  |  |  |  |  |  |  |
| Adverse events (before/after each session by the AEP) |  |  | x | x | x | x | x | x | x | x |
| **EFFICACY** |  |  |  |  |  |  |  |  |  |  |
| Accelerometry (worn for 5 days prior to randomisation) |  | x |  |  |  |  |  |  |  |  |
| SIMPAQ |  | x |  |  |  |  |  |  |  |  |
| Preferences, Barriers, Motivators Questionnaire |  | x |  |  |  |  |  |  |  |  |
| WHO DASS 2.0 |  | x |  |  |  |  |  |  |  | x |
| BPRS |  | x |  |  |  |  |  |  |  | x |
| SANS |  | x |  |  |  |  |  |  |  | x |
| BREQ 3 |  | x |  |  |  |  |  |  |  | x |
| Physical Capacity (6MWT, 30 sec sit-to-stand, grip strength, push up test) |  | x |  |  |  |  |  |  |  | x |
| Physical Health measures (BP, height, weight, waist circumference) |  | x |  |  |  |  |  |  |  | x |
| 12RM strength, chest press and squat(RT only) |  | x |  |  |  |  |  |  |  | x |
| SEES |  |  |  |  | x |  |  |  |  | x |
| **INTERVENTION SESSIONS** |  |  |  |  |  |  |  |  |  |  |
| RT and AIT (x3 sessions per week) |  |  | x | x | x | x | x | x | x | x |
| Health Coaching Sessions offered |  |  | x |  | x |  | x |  | x |  |
| **ACCEPTABILITY** |  |  |  |  |  |  |  |  |  |  |
| Acceptability questionnaire |  |  |  |  |  |  |  |  |  | x |
|  |  |  |  |  |  |  |  |  |  |  |
| Individual interview (RT condition) - optional |  |  |  |  |  |  |  |  |  | x |

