**7.1.1 Resistance training Intervention (RT)**

The World Health Organisation and Australian Physical Activity Recommendations suggest resistance training to occur on 2 or more days per week, involving main muscle groups (9, 10).

The intervention will involve resistance training three days per week, using a variety of resistance training equipment such as hand weights and resistance bands appropriate for small clinical gym settings to enable replication of the study without substantial investment in specialised equipment or gym spaces.

There will be a 10 minute stretching warm up and 5 minute cool down. The resistance training intervention will take approximately 30 minutes duration, with total duration 45 minutes. The active exercise volume will be progressed to 40 minutes by week 4 of the intervention, with a total duration of exercise being 50-55 minutes.

Resistance training will be progressive and tailored to the individual participant’s current ability/ exercise capacity and exercise history via individually prescribed programs, taking into account participants with schizophrenia who may be deconditioned and may have little experience with resistance training. At all times training will be tailored to their experience level by experienced AEP’s trained exercise prescription. An initial assessment of muscle strength will be assessed using the 12 repetition maximum test (12-RM) for relevant large muscle groups to guide exercise prescription, which is an appropriate proxy measure to estimate the 1-RM (1 Repetition Maximal test) in poorly conditioned individuals, using an established conversion formula; Brzycki 1RM Formula, 1RM = Weight x (36 / (37 – Repetitions),(11).

The aim will be to increase muscle strength progressively over the 8 weeks. Training will be appropriate for beginners and be aimed at moderate intensity (40-70%) of estimated maximum strength, (1-RM). Week 1 will start with 40% of 1-RM, and progressed with 5% increments each week as per capacity of the individual, with 3 sets of 8-10 repetitions, of approximate 40 seconds duration per set, and a 90 seconds duration between sets.

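### The RT-only 12RM test is placed in a baseline battery completed before randomisation and run by blinded assessors; these statements cannot all be followed, and at week 8 the test can reveal allocation to the raters

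*Protocol*

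**What the plan says.** Five places in the protocol bear on this test.

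- **Who gets it.** Section 6, item 11 of the list of measures, restricts the squat and chest-press 12RM to one arm: "in the RT group only (due to the complexity of the testing". It is to be measured before and after the intervention.
- **When.** The Table 1 row "12RM strength, chest press and squat(RT only" is marked at Visit 1 (baseline, week 0) and Visit 9 (week 8).
- **Order relative to randomisation.** The paragraph introducing the battery states "Baseline assessments will be conducted prior to randomisation". Section 7.1.5 agrees: "Participants will be randomised once written consent has been obtained and the baseline assessments have been completed".
- **By whom.** Section 6 opens with "Trained research assistants, who are blind to group membership, will conduct all assessments". Section 3, under Feasibility Criteria, adds "All outcome raters will be blind to outcome allocation" and accepts that participants cannot be blinded.
- **What else it is for.** Section 7.1.1 describes an initial strength test "using the 12 repetition maximum test (12-RM) for relevant large muscle groups to guide exercise prescription". It does not say who performs the test or whether it comes before or after allocation.

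Section 11.4 analyses the 12RM within the RT arm only, by a paired t test of pre against post.

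**The concern.** There are two linked problems. First, the baseline test is defined by membership of an arm that has not yet been assigned. Sites would have to improvise, either by testing everyone or by testing after allocation, and different sites could choose differently. The pre-value is one half of the planned paired comparison and also feeds the 1-RM estimate used in section 7.1.1, so its timing should not be left open.

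Second, a test done in one arm only discloses the arm to whoever is told to run it or leave it out. RT is revealed by the presence of the test and AIT by its absence. Participants know their own arm, so the single-blind design in section 3 rests on the assessors. At stake are the between-arm secondary comparisons at week 8 that depend on an interviewer or tester: BPRS and SANS, the interviewer-administered WHODAS 2.0, and effort tests with encouragement such as the 6MWT. Section 7.1.5 has an independent staff member announce allocation so that the research team stays blind. The 12RM schedule could undo that precaution.

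**Working it through.** No formula applies to the contradiction itself. The check is whether the statements can all be true together.

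**Baseline**

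1. The test is for RT participants only (section 6, item 11; Table 1).
2. It is due at baseline, week 0 (Table 1).
3. Baseline assessments come before randomisation (section 6).
4. Randomisation waits until baseline assessments are complete (section 7.1.5).

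By 3 and 4, nobody belongs to the RT group when baseline is done. Statement 1 then cannot be applied at the time fixed by statement 2. Testing everyone breaks statement 1. Testing after randomisation breaks statements 3 and 4 unless the 12RM is exempted, and no exemption is written.

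**Week 8**

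5. The test is for RT participants only and is due at week 8 (Table 1).
6. Blinded research assistants carry out all assessments (section 6).
7. All outcome raters are blind (section 3).

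To carry out 5, the person responsible must know who is in RT. Under 6 that person is a blinded assistant, so 5 and 6 conflict. Whether 7 also fails for a given participant's outcomes depends on two things the protocol does not fix:

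- whether the assistant handling the 12RM is also that participant's rater;
- whether the ratings are complete before the assistant runs the test or learns that it is due.

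Table 1 columns are weeks and give no order of tests within week 8.

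Moving only the first test does not settle this. If the same assistants ran it after allocation, they would know the arm from the start of the trial, and a favourable order of tests at week 8 would no longer protect the ratings. Timing and tester have to be changed together.

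**How many ratings could be affected**

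Section 11.3 plans 50 participants, about 25 per arm, with 20% drop-out per condition: 25 × (1 − 0.20) = 20 per arm, or about 40 participants with week-8 ratings. This is an upper bound on exposure under the planned drop-out. It is not an estimate of bias. Participants withdrawn from the intervention are also asked for post measures where possible (section 9.1), so the count could be somewhat higher.

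The protocol gives no information from which the shift caused by an unblinded rater could be derived, so no bias figure is offered.

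**The case against.** The strongest defence is that the intended practice is probably workable. Item 11 speaks of before and after the intervention, which would allow a test after allocation and before the first session. The introductory sentence does not govern every listed item, since SEES (item 10) is taken at weeks 3 and 8 and has no baseline. In Table 1 only the accelerometry row states that it precedes randomisation. The prescription use in section 7.1.1 points towards a test after allocation, perhaps by the exercise physiologist. All of this is fair, and it shows that the problem is one of wording and scheduling. It does not remove the conflict: Table 1 puts the test in the baseline column, section 7.1.5 completes baseline before randomisation, and nothing exempts the 12RM from the rule that blinded assistants do everything.

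A reader might also infer several stronger things that the protocol does not support.

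- **That week-8 unblinding is certain.** It depends on who runs the test and in what order.
- **That assessor blinding is the only guard against rater bias.** Section 6 also specifies a semi-structured interview guide and anchored scoring for the BPRS, and an interview guide for the SANS.
- **That WHODAS is a rater-scored scale like the other two.** It is an interviewer-administered questionnaire.
- **That the exercise physiologist already performs the initial 12RM.** Section 7.1.1 names no tester.
- **That the main result is compromised.** Recruitment, retention and attendance do not depend on blinded ratings, and the sample size rests on feasibility.

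**Conclusion.** The point holds as an internal contradiction with a conditional consequence. As written, the 12RM cannot be RT-only, done at baseline and completed before randomisation all at once. It also cannot be RT-only at week 8 while staff who are to stay blind carry out every assessment.

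The single-blind commitment fails for a participant's secondary outcomes if the assistant handling the 12RM is also that participant's rater and the ratings are not yet complete when the arm becomes known. The protocol neither requires nor prevents that combination, although having the same group of assistants do all assessments makes it the natural result of following the text.

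Up to about 20 participants per arm could be exposed at week 8 under the planned drop-out. The size of any bias is unknown. The outcomes concerned are secondary ones in an exploratory feasibility trial, so this is something that should be fixed rather than a flaw that threatens the primary conclusions.

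**What to change.** Reconcile section 6 (opening statement, introduction to the battery, item 11), section 7.1.5 and Table 1:

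1. Exempt the 12RM explicitly from the blinded, pre-randomisation battery.
2. Schedule the first test after randomisation and before RT loading starts, which fits its prescription use in section 7.1.1, and show it in Table 1 as separate from the baseline visit.
3. Name the tester, who must not be an outcome rater. The site exercise physiologist, who supervises the sessions, is one possibility; the protocol does not currently assign the task.
4. Place the week-8 test after that participant's blinded ratings are complete.
5. Record the 12RM on a form the raters do not see.

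As a precaution, also keep the answer on whether participants are happy with their allocation (section 7.1.5, recorded in the CRF) off any form the raters see. Section 12 has the CRF hold the clinical assessments too. The protocol does not say that raters see this answer, so this is preventive only.

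**Cost.** A protocol amendment with ethics approval (section 16.7) and one separate form. There is no new test, no change to the sample size and none to the primary analysis. Whether it needs extra staff time depends on who does the test now, which the protocol does not say. The downside is that a within-RT measure is recorded by unblinded staff, which is unavoidable for a test given in one arm only.
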